#### Specific management of the intervention group

The intervention will begin upon admission to the intensive care unit and
will continue for 24 hours after arrival at the ICU. The MAP target of the
intervention group will be 85 - 90mmHg in the first 24 hours after surgery.
The MAP will be measured using an invasive blood pressure catheter, measured
at 1-hour intervals during the first 12 hours and at 2-hour intervals
thereafter until the 24 hours have been completed (according to the protocol
of the ICU). Patients with a MAP lower than the established target may
receive fluids or vasopressors according to the discretion of the attending
physician to achieve the established target MAP.

Noradrenaline will be the initial vasopressor of choice, and the second will
be determined by the attending physician. In hypotensive patients with
reduced cardiac output as monitored by pulmonary artery catheter or
transthoracic echocardiogram, inotropes may be used at the discretion of the
assistant team. Patients who naturally present with a MAP > 90 mmHg even
after complete weaning from vasopressors will not receive additional
vasodilators to reduce the MAP to the study target. The use of vasodilators
in hypertensive patients for the purpose of blood pressure control will be
determined according to the decision of the attending physician.

#### Specific management of the control group

Patients in the control group will undergo the care regimen described above,
the only difference being the target MAP, which in this group will be 65 -
70mmHg during the first 24 postoperative hours. The MAP will be measured
using an invasive blood pressure catheter. Patients who naturally present
with a MAP > 70mmHg even after complete weaning from vasopressors will
not receive vasodilators to reduce the MAP to the target range. The use of
vasodilators in hypertensive patients for the purpose of blood pressure
control will be determined according to the decision of the attending
physician. The MAP will be measured using an invasive blood pressure
catheter at the same intervals described for the intervention group.

### Serious or unexpected adverse events

Any adverse events identified to be related to the study intervention, whether
serious or unexpected, as assessed by researchers or professionals involved in
the care will be immediately reported to the competent authorities, in
particular to the management of the unit, the management of the hospital and the
responsible REC. The patient will receive all necessary care to reverse or
minimize any damage resulting from the study. Given the suspicion of such
events, if the patient is in the intervention group, the intervention will be
interrupted, and the data will be analyzed according to an intention to treat
protocol, except in cases in which the patient or family members request
withdrawal of the individual from the study. We believe that safety should be
the priority in a randomized clinical trial. The absence of an external
committee in our study is the result of extensive discussion in the design of
the study, in which the safety of the intervention chosen and the additional
costs that the committee would represent to the project were considered. The
final decision not to include a monitoring committee was defined, described and
sent to the REC responsible for the original project.

### Data collection

The following data will be collected from all patients: name, sex, age, race,
height, weight, hospital identification number, date of birth, etiological
diagnostic indicator of transplantation, pretransplantation Model for End-stage
Liver Disease (MELD) score, origin before transplantation (ICU, ward or home),
comorbidities (diabetes mellitus, heart failure, arterial hypertension,
nondialytic chronic renal failure, active cancer, previous stroke or transient
ischemic attack or immunosuppressive therapy in the last 30 days before
surgery), preoperative creatinine, donor risk index (DRI) and use of nephrotoxic
drugs in the week before transplantation.

The following intraoperative data will also be collected: anesthesia time, total
and cold ischemia time of the liver graft, presence of ischemia‒reperfusion
syndrome, time of admission to the ICU, use of blood products, antibiotic
prophylaxis, initial value of arterial lactate, peak arterial lactate, final
value of arterial lactate, use of basiliximab, use of fluids, type of fluids,
episodes of intraoperative hypotension and loss of fluids.

The following postoperative data will also be collected: length of hospital stay
after transplantation; length of stay in the ICU; time of mechanical
ventilation; duration of vasopressor use and maximum vasopressor dose; need for
renal replacement therapy; need for postoperative transfusion; primary graft
dysfunction; secondary graft dysfunction; need for retransplantation; surgical
site infection; Sequential Organ Failure Assessment (SOFA) score on admission to
the ICU; D1, D3 and D7; daily creatinine, to evaluate the presence of acute
kidney failure (AKI) in the first 28 days after transplantation or until
hospital outcome if this occurs before the described period; admission and
48-hour urinary NGAL; presence of surgical site infection in the first 7 days
after transplantation; arrhythmias requiring chemical or electrical treatment in
the first 7 days after transplantation; diagnosis of acute coronary syndrome in
the first 7 days after transplantation; volume of crystalloids infused in the
first 24 hours after surgery; volume of colloids infused in the first 24 hours
after surgery; diuresis in the first 24 hours after surgery; drainage output in
the first 24 hours after surgery; presence of major bleeding in the first 24
hours after surgery; need for transfusion in the first 24 hours after surgery;
antibiotic prophylaxis in the first 24 hours after surgery; use of nephrotoxic
drugs in the first 7 days; immunosuppression in the first 7 days and maximum
tacrolimus level within 7 days; new surgery within 7 days after randomization;
ICU readmission for treatment of complications within 7 days after
randomization; need for retransplantation within 28 days and ICU and hospital
outcome in 28 days (discharge, hospitalization or death).

Data collection will be performed by an external professional (research nurse)
with no connection to the unit. This professional will have access to the data
described but will not have any role in the randomization and management of
patients participating in the study. Such data will be collected in an
electronic form via Redcap® and will remain protected by a
nontransferable password. The professional will perform serial evaluations to
ensure the follow-up of all patients until the 28th postoperative day. The final
result collected will be available, also by means of a password, to the external
professional in charge of the statistical calculations, as well as to the main
researcher.

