### Other outcomes (safety)

The safety outcomes to be assessed are the incidence of major postoperative
bleeding at 7 days, transfusion of blood components at 7 days and incidence of
arrhythmias requiring drug or electrical therapy at 7 days.

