□ **Acute renal dysfunction according to urinary NGAL assessment**

Number of days during the first 7 postoperative days that the patient was alive
and did not meet the following criteria for renal dysfunction: urinary NGAL
value > 150ng/mL. This outcome will be assessed at admission and at 48
hours.^(2)^

□ **Primary graft dysfunction - initial poor function subtype at 7
days**

Development of one of the following laboratory criteria within the first 7 days
after liver transplantation: bilirubin > 10mg/dL on the seventh day after
transplantation; international normalized ratio > 1.6 on the seventh day
after transplantation; alanine aminotransferase or aspartate aminotransferase
> 2,000IU/L in any of the first 7 days after transplantation.^(3)^

□ **Primary allograft dysfunction - primarily nonfunctional subtype at 10
days (Broering)**

Need for retransplantation in the first 10 days after transplantation or death
due to a nonfunctioning graft.^(3)^

□ **Major adverse kidney events in 28 days (MAKE28)**

The incidence of death, need for renal replacement therapy or persistent renal
dysfunction at 28 days after liver transplantation.^(4)^

□ **Days alive and hospitalization-free in 28 days**

Number of days among the first 28 postoperative days in which the patient was
alive and hospitalization-free.

□ **Major postoperative bleeding at 7 days**

Dichotomous outcome of bleeding that indicates, on the same day, the transfusion
of more than two units of packed red blood cells or the need for surgical
intervention indicated in the first 24 postoperative hours.

□ **Transfusion of blood components in 7 days**

Number of blood components transfused in 7 days separated into packed red blood
cells (one unit equal to one bag), fresh frozen plasma (one unit equal to one
bag), fibrinogen concentrate (one unit equal to 1g) and tranexamic acid (one
unit equal to 1g).

□ **Arrhythmias requiring chemical or electrical therapy within 7
days**

Description in the prescription or medical records of antiarrhythmic or
electrical cardioversion therapy for the first 7 days for treating abnormal
rhythm. A maximum of one event per patient will be considered dichotomously, as
the same event can be reentrant.

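### Major bleeding is named as a 7-day safety outcome but is collected, and at least in its surgical limb defined, for 24 hours only; the 7-day transfusion count has no matching dated item and omits platelets

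*Protocol article*

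**What the plan says.** Three parts of the protocol article bear on this.

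- **Other outcomes (safety)** lists major postoperative "bleeding at 7 days, transfusion of blood components at 7 days and incidence of" treated arrhythmias, the last also at 7 days.
- **Appendix 1** has an entry for major bleeding titled as a 7-day outcome. It has two limbs: over two red-cell units transfused on one day, or surgical "intervention indicated in the first 24 postoperative hours". The transfusion entry is a 7-day number of units, split into red cells, fresh frozen plasma (one unit per "bag), fibrinogen concentrate (one unit equal to 1g) and tranexamic acid (one" unit again being 1 g). No other component is named.
- **Data collection** has one postoperative bleeding item, followed directly by a transfusion item: "presence of major bleeding in the first 24" "hours after surgery; need for transfusion in the first 24 hours after surgery". Transfusion appears once more, as "need for postoperative transfusion", with no window. The same list also has "new surgery within 7 days after randomization", without an indication.

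**The concern.** The title of the bleeding outcome, its definition and its data item do not share a window. A condensed article may leave form-level detail elsewhere, but here the stated windows conflict, and the first conflict lies inside a single Appendix entry.

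This matters because the article provides for no external monitoring committee and no interim analysis. Its adverse-event reporting covers events that staff who know the allocation judge related to the intervention. The prespecified safety outcomes therefore carry much of the unselected comparison between arms. The Comments section hopes to describe a potentially safe tool. A statement that bleeding at 7 days did not differ would not be supported by data and a definition that stop, wholly or partly, at 24 hours.

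**Working it through.** The article gives no bleeding or transfusion rate and no timing of bleeds, so there is no figure of its own to reproduce. The check is a comparison of texts.

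**1. Major bleeding: which events count?** The 24-hour limit in the Appendix sentence can be read narrowly (surgical limb only) or widely (both limbs).

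| Event | 7-day outcome as titled | Definition, narrow reading | Definition, wide reading | Listed 24-hour bleeding item |
|---|---|---|---|---|
| First 24 h: over two red-cell units in a day | event | event | event | recorded |
| First 24 h: surgery for bleeding | event | event | event | recorded |
| Days 2-7: over two red-cell units in a day, with or without surgery | event | event | not an event | not recorded |
| Days 2-7: surgery for bleeding, two or fewer units that day | event | not an event | not an event | not recorded |

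The fourth row is lost on either reading of the definition. The third is lost on the wide reading. On the narrow reading it is an event by definition, but the listed bleeding item would not capture it.

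**2. Can another item recover the late events?** The 7-day item on new surgery would register the operation in row four. With no indication listed, it cannot separate bleeding from other reasons, and the definition would still exclude the event. It says nothing about late transfusion without surgery.

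**3. Transfusion: does the data list supply the outcome?** The outcome is a count of units, by component, over 7 days. One listed item is a need within 24 hours; the other is a need with no window. Neither is described as a count, by component, or to day 7.

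**4. Component list.** It has four entries: red cells, plasma, fibrinogen concentrate and tranexamic acid. The last is a drug. Platelets, a blood component, are absent.

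**5. Is this just condensation?** The same list dates arrhythmia, surgical site infection, acute coronary syndrome and new surgery to 7 days. Arrhythmia, the third safety outcome, matches its named window; bleeding does not.

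**6. Size.** Let f be the share of true 7-day events that is captured, assumed equal in both arms. Observed risks are f·p1 and f·p0. Their ratio is unchanged, their difference is multiplied by f, and there are fewer events. Because f, p1 and p0 are not in the article, no number can be put in. The fact that 24 hours is one seventh of the window is a share of time, not of events.

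**7. How far along was the trial?** 67.8% of 174 is 0.678 × 174 ≈ 118 patients by the end of February 2023, so a change would need back-fill.

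**The case against.** The strongest reply is that the transfusion outcome is consistently 7 days in both the safety section and Appendix 1, and that the undated item may be the general record, with the 24-hour item as a subset. Surgical site infection and retransplantation also appear both undated and dated. This stands. A reader might infer that transfusion is collected for 24 hours only, but the article does not say so. What remains is that no dated 7-day unit count is listed.

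Other stronger readings also fail:

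- *Re-operation after day 1 is never an event.* On the narrow reading, one with over two red-cell units on the same day still counts.
- *These tables are the only comparative evidence on bleeding.* New surgery to 7 days is also collected.
- *Bleeding is the main expected harm of the higher pressure target.* The article does not rank its three safety outcomes.
- *Bleeding is under-counted by a known amount.* Loss follows only if the form matches the list, and its size is unknown. With equal capture in both arms, the direction of an effect is not hidden.
- *The component list distorts the bleeding outcome or inflates a total.* Major bleeding uses red cells only, and components are reported separately. Tranexamic acid is a labelling slip; the missing platelets are a gap in the transfusion count alone.

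It can also be argued that a 24-hour bleeding measure is coherent, because the pressure targets last 24 hours. That is fair, but it would be a different outcome from the one named.

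**Conclusion.** The point holds in this limited form. Major bleeding is named for 7 days, while its only listed postoperative data item, and at least its surgical limb, cover 24 hours. Followed as written, the plan does not deliver the named outcome. The 7-day transfusion count lacks a matching dated item, and its closed list includes a drug and leaves out platelets.

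Confidence is high for the conflict between the texts. The practical loss depends on whether the actual form follows the published list, which the article does not show. The primary outcome and the sample size are untouched. It should be put right before analysis.

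**What to change.** Reconcile the safety section, Data collection and Appendix 1 before analysis, by a dated and documented change made without sight of results by arm.

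- **Major bleeding.** Apply the named 7-day window to both limbs, and report the 24-hour version separately. If only the first 24 hours can be recovered, rename it a 24-hour outcome and make no 7-day claim.
- **Data items.** From charts, by day for days 1-7, record units of each component including platelets, and any re-operation with its date and indication. Back-fill patients already enrolled.
- **Tranexamic acid.** Report it as a drug, outside the component counts.

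The cost is a few extra form fields and chart review for the roughly 118 or more patients already randomized. The research nurse already follows every patient to day 28, so no new visit or test is needed.

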### Data handling and record keeping

The confidentiality of the information related to the participants will be
protected by the team involved in the conduction of the research project, and
the identity of the patients will at no time be revealed, as provided in
Resolution 466/12 of the National Health Council, item III.2.i, and other
legislation in force. The data will be stored electronically with access
protected by a password.

### Sample size calculation

Based on the primary outcome incidence of 73.7% (acute renal dysfunction within 7
days) obtained from a database of the same population and location, 174 patients
will be required to demonstrate an absolute reduction of 20% in the primary
outcome, with a power statistic of 80% and alpha of 5%. The data used for this
calculation were obtained by calculating the incidence of AKI based on an
increase in serum creatinine by 1.5 times the baseline value. The criterion used
to choose the effect (20% absolute reduction in the AKI outcome) was chosen
based on the principle of clinical relevance. All patients selected for
transplantation will be evaluated regarding the inclusion and exclusion criteria
and will be informed of the study in a standardized way if able to
participate.

### Statistical analysis

The analyses will be performed according to the “intention-to-treat” principle;
all randomized patients will be included in the analysis according to the
treatment group to which they were randomly assigned. Summary statistics per
group, with treatment effects, 95% confidence intervals and p values, will be
presented for the primary and secondary outcomes. Continuous variables will be
tested for normality using the Shapiro‒Wilk test after graphic analysis by
histogram. Parametric continuous variables between two groups will be compared
with the unpaired *t* test and within the same group with the
paired *t* test. If analysis among more than two groups is
required, analysis of variance (ANOVA) will be used. Nonparametric continuous
variables will be evaluated using the Wilcoxon test or the Mann‒Whitney U test
between two groups and the Kruskal‒Wallis test between three or more groups.
Categorical variables will be evaluated using the chi-square test or Fisher’s
exact test, as appropriate. P values < 0.05 will be considered statistically
significant. The outcomes of hospitalization-free days or renal dysfunction over
time will be calculated based on the 7- and 28-day follow-up, respectively,
using Cox regression models. The calculations of survival curves will be
performed with the Kaplan‒Meier method. For the statistical analysis of
outcomes, the results will be adjusted for previous renal function, and logistic
regression will be used to adjust for other confounding factors that generate
inconsistency in the baseline that were not corrected by the randomization of
the study (use of nephrotoxic drugs, maximum tacrolimus level in the first week,
intraoperative fluid balance and intraoperative major bleeding). No statistical
adjustments will be provided for multiple comparisons in the case of secondary
outcomes, and therefore, we suggest that these be interpreted as exploratory
analyses.

The existence of missing data will be described in the publication and managed
with simple exclusion from the analysis. For this study, no interim analyses are
foreseen.

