### Secondary objective

To evaluate whether higher (85 - 90mmHg) *versus* usual MAP levels
(65 - 70mmHg) in the first 24 hours after liver transplantation surgery are
associated with 28-day mortality; retransplantation in 28 days; renal
replacement therapy in 7 days; surgical site infection within 7 days; days alive
and free of renal dysfunction in 7 days; renal dysfunction according to the
values of neutrophil gelatinase-associated lipocalin (NGAL) at admission and
after 48 hours; length of stay in the ICU; length of hospital stay; days alive
and hospitalization-free in 28 days; liver graft dysfunction (initial poor
function subtype) in 7 days; liver graft dysfunction (primary nonfunction) at 10
days and major adverse kidney events at 28 days (MAKE28).

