## APPENDIX 1 DEFINITIONS OF OUTCOMES

**Protocol:** Comparison between different mean arterial pressure
targets in patients undergoing liver transplantation in an open-label,
controlled, single-center, randomized clinical trial.

□ **Acute renal dysfunction**

Only patients with an increase in serum creatinine by 1.5 times the baseline
value (last value prior to transplantation) will be considered to have renal
dysfunction according to the adaptation of the KDIGO criterion referenced in the
main text. For this, the diuresis criterion was ignored, as it can be difficult
to interpret the real meaning of these data in the postoperative period and in
cirrhotic patients. An increase of 1.5 times was used instead of the criterion
of an increase of 0.3mg/dL because the calculated sample was based on the
criterion of 1.5 times the baseline creatinine.^(1)^

□ **Death within 28 days**

Death within the first 28 days after liver transplantation.

□ **Retransplantation in 28 days**

Conduction of a new liver transplantation within the first 28 days after the
initial transplantation.

□ **Renal replacement therapy in 7 days**

Administration of renal replacement therapy in the first 28 days after liver
transplantation by any modality, prescribed by a specialist team of the
institution itself, based on the classic indications (refractory hyperkalemia,
refractory hypervolemia, refractory acidosis, refractory hypernatremia or
uremia). Patients undergoing renal replacement therapy for ammonia clearance
will not be considered.

□ **Surgical site infection**

Infection at the site of the surgical incision that appears to be related to the
surgical procedure, manifesting as purulent secretion through a drain placed in
the incision of the organ/cavity; organisms isolated from a positive culture of
secretions or tissue of the organ/cavity obtained aseptically; presence of
abscess or other evidence of infection, involving the organ/ cavity, identified
in direct examination, during a new surgery, or through histocytopathological
examination or imaging, which results in surgical approach and/or initiation of
a new regimen of antibiotic therapy, as indicated together by the surgical and
infectious diseases teams.

□ **Days alive and free of renal dysfunction in 7 days**

Number of days during the first 7 postoperative days that the patient was alive
and did not meet the criteria for renal dysfunction consistent with the primary
outcome

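### Two secondary outcomes defined as counts of days alive and free are assigned to Cox regression, with their 7-day and 28-day windows reversed

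*Protocol article*

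**What the plan says.** The sentence at issue is in the Protocol article, Statistical analysis. It opens with "The outcomes of hospitalization-free days or renal dysfunction over" and continues "time will be calculated based on the 7- and 28-day follow-up, respectively", then names the model: "using Cox regression models".

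Appendix 1 names the renal outcome "Days alive and free of renal dysfunction in 7 days" and defines it as "Number of days during the first 7 postoperative days that the patient was alive" and did not meet the renal dysfunction criterion of the primary outcome. It names the hospital outcome "Days alive and hospitalization-free in 28 days" and defines it as "Number of days among the first 28 postoperative days in which the patient was" alive and out of hospital. The Secondary objective lists both outcomes with these same windows.

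The Statistical analysis section also sets general rules: a t test for normally distributed continuous variables, and a Wilcoxon or Mann-Whitney test otherwise. It promises treatment effects, 95% confidence intervals and p values for all secondary outcomes, and describes those outcomes as exploratory because no multiplicity adjustment is made.

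**The concern.** There are two separate faults in one sentence.

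First, the word linking the two outcomes to the two windows makes the order binding, and the order is the opposite of the article's own definitions. Followed as written, it would assess hospital-free time over a week and renal dysfunction over four weeks.

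Second, the model does not fit the quantity. Each outcome is a bounded count, 0 to 7 or 0 to 28, in which days after death earn nothing. Cox regression needs a time to a defined event and a censoring rule. Time to first renal dysfunction largely repeats the primary outcome and drops duration and recovery, which are the main things that the day count adds. A hazard ratio for discharge is not a comparison of days alive and out of hospital.

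At stake is whether the reported estimates for these two outcomes describe what the article says they describe.

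**Working it through.** **Figures not in dispute.** The sample size is unaffected. From Sample size calculation, with incidences 0.737 and 0.737 − 0.20 = 0.537, 80% power and alpha 5% (two-sided assumed), the unpooled formula gives n per arm = (1.960 + 0.842)² × [0.737 × 0.263 + 0.537 × 0.463] / 0.20² ≈ 7.849 × 0.4425 / 0.04 = 86.8. That is 87 per arm, or 174, as stated.

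**Windows side by side.**

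| Outcome | Secondary objective and Appendix 1 | Statistical analysis, as written |
|---|---|---|
| Renal dysfunction | 7 days, count 0–7 | 28 days, Cox |
| Hospitalization-free days | 28 days, count 0–28 | 7 days, Cox |

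**Model against definition, renal.** Take one survivor with dysfunction on days 1–2 and another with dysfunction on days 1–7. Free days are 7 − 2 = 5 and 7 − 7 = 0. Both have a first event on day 1, so they contribute the same information to a first-event Cox model.

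**Model against definition, hospital.** Take one patient who leaves on day 10 and stays out, and another who leaves on day 10 and is back in hospital on days 13–28. Free days are 28 − 10 = 18 and 12 − 10 = 2. Time to first discharge is identical.

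**What the wrong hospital window could do (illustration).** The article gives no length of stay. Assume a log-normal stay with log-SD 0.6, so P(stay ≤ t) = Φ[(ln t − ln median)/0.6], deaths ignored. For a median of 14 days and t = 7 this is Φ(−0.693/0.6) = Φ(−1.155) = 12%.

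| Assumed median stay | Out by day 7 | Out by day 28 | Mean free days, 7-day window | Mean free days, 28-day window |
|---|---|---|---|---|
| 10 days | 28% | 96% | 0.5 | 16.4 |
| 14 days | 12% | 88% | 0.2 | 12.6 |
| 18 days | 6% | 77% | 0.1 | 9.6 |

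Now add an assumed 25% shorter median stay in one arm and 8% deaths in both, scored as zero days (87 per arm, 1,000 replicates). Mann-Whitney power with the 28-day window is 74.1%, 74.3% and 76.5% for medians of 10, 14 and 18 days. With the 7-day window it is 68.7%, 50.9% and 39.2%.

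**What a first-event model could do to the renal count (illustration).** The simulation used 174 patients and 2,000 replicates, with assumed onset on days 1–4, geometric duration and 3% deaths. It compared a log-rank test of first dysfunction (the Cox score test) with a Wilcoxon test on free days.

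- No effect: 4.9% and 4.7% rejections.
- Only duration falls, mean 4.5 to 3.0 days: 5.0% against 29.1%.
- Only incidence falls: 76.3% against 62.7%.

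Runs of closely similar models gave 4% to 6% against 26% to 28% for the same duration shift. With a smaller shift, 4.5 to 4.0 days, the gap vanished (5% against 6%).

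**The case against.** The strongest defence is that the sentence refers to renal dysfunction over time, not to the named count of dysfunction-free days. The Data collection section records daily creatinine for up to 28 days, and MAKE28 includes persistent dysfunction at 28 days. A 28-day Cox model of time to renal dysfunction would then be legitimate, and the day count would fall under the general rule. This is a possible reading, but it does not clear the text. No time-to-renal-dysfunction outcome is listed in the Secondary objective or Appendix 1, the primary outcome and the day count both run to 7 days, and creatinine collection stops at the hospital outcome if that comes earlier. Nor does this reading rescue a 7-day window for hospitalization-free days.

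It can also be said that the reversal is a word-order slip, since the windows agree everywhere else. That is likely, and swapping two numbers cures it. The mismatch of model and outcome remains.

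Three stronger inferences are tempting and are not supported:

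- A reader might conclude that neither outcome would be analysed at all. The section promises effect estimates for every secondary outcome and already contains a Mann-Whitney rule. The fault is that a specific sentence competes with a general one and nothing says which governs.
- A reader might conclude that deaths would be censored as if those patients could still go home, favouring an arm with early deaths. The article states no censoring rule, and such detail may sit in a document not shown. It is a risk of the usual default, not something the plan prescribes.
- A reader might take it as fact that almost nobody would have hospital-free days in the first week. The article gives no stay data, and with an assumed 10-day median 28% would be out by day 7.

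The power comparison does not show that Cox is generally the weaker method. In the incidence-only case, which is closer to the trial's hypothesis, the first-event analysis has more power. The objection to it is that it answers a different question.

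**Conclusion.** The point stands as an internal contradiction over windows and a mismatch between the named model and the defined outcomes. Both follow from the text alone and need no assumption. The size of the consequence does need assumptions: the free-day and power figures depend on length of stay, onset, duration and death rates that the article does not give, and serve only as illustration.

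The reach is two secondary outcomes that the article itself calls exploratory. The primary outcome, its 7-day window and the sample size are untouched, so a reader should not infer any threat to the trial's main conclusion. Exploratory status excuses the absence of multiplicity control; it does not excuse estimating a different quantity over a different window. This should be fixed, but it is not critical.

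**What to change.** In Statistical analysis, replace the sentence so that it does three things:

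- Assigns 7 days to days alive and free of renal dysfunction, and 28 days to days alive and hospitalization-free.
- States that both are computed per patient as day counts, with zero days credited after death, and compared with the rank-based test already in the plan, together with a difference in days and its 95% confidence interval. Proportional-odds regression or a bootstrap interval are acceptable options, not requirements.
- Keeps Cox regression only for any time-to-event outcome that is separately defined, with the event, the censoring rule and death as a competing event stated.

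The cost is a wording change and minor programming, with no extra data. The article reports 67.8% of the sample reached by 28 February 2023 and foresees no interim analysis, so on that status the correction could be made before outcomes are compared by arm.
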